### Procedures

#### Recruitment

Six recruitment strategies are being utilized to ensure enrollment targets are met and a diversity of participants are enrolled: (1) *online*: banners advertisements and digital flyers are placed through geo-mapping on relevant websites and social media platforms; (2) *print media*: advertisements are placed in local print media for trans women and SMM; (3) *outreach*: two research assistants conduct outreach in identified areas where trans women and SMM who use substances congregate, including bars/clubs, motels, parks, street corners, mini markets, boutiques, wig shops, electrolysis offices, salons, lingerie stores, bathhouses, and sex clubs (outreach locations are continually modified through ongoing community mapping and input from the [CAB]); (4) *posters and club cards*: are displayed/distributed throughout the study site and collaborating clinics, organizations in the LAC area serving trans women or SMM, and at dance clubs, bars, and community events; (5) *in-reach*: several service programs operate at the study site that cater to trans women and SMM who use substances; and (6) *long-chain referral*: current study participants are asked to recruit a maximum of 3 potential new participants, and then receive an incentive when an eligible potential participant enrolls.

#### Randomization

Stratified block randomization with random block sizes is used to assign participants to each of the two initial study arms (stepped care vs. SOC, 3:1 ratio) and to assign non-responding participants at the 3-month visit to the two stepped care modalities (*A.S.K.-PrEP* + CM vs. CM alone, 1:1 ratio). To ensure balance with respect to certain covariates, participants are grouped into four strata: (1) SMM < 35 years and/or African American/Black; (2) SMM > 34 and non-African American/Black; (3) trans women < 35 years and/or African American/Black; (4) trans women > 34 and non-African American/Black. Blocked randomization lists are generated separately for each strata by generating a block of random size (block size = 4, 8, or 12 at baseline; block size = 2, 4, or 6 at 3 months).

#### Incentives

All participants are compensated $15 for the screener; $50 for the baseline and 3-month follow-up assessment, with an additional $25 bonus for completing within +/- 7 days of the exact 3-month due date; $75 for the 6- and 9-month follow-up assessment; and $100 for 12-month follow-up assessment. Incentives are provided in gift cards; participants are not given cash. Participants are offered a drink (e.g., water, soda, or juice) and a snack (e.g., granola bar, box of raisins, bag of chips) during each assessment data visit.

### Measures

All assessments have been used in prior studies; some have been modified and tailored by our group for trans women and SMM who use substances (see Table 4) [23, 58]. Assessments were chosen to minimize participant burden while addressing study aims, and are estimated to take 45–60 min at baseline, and 30–45 min at each follow-up time point. All assessments will be collected using Audio Computer-Assisted Self-Interview.

**Table 4 Tab4:** Assessments, corresponding aims, variables, and Time points

Assessment Instrument	Aims	Variables	Screening	Baseline	3-mo F-U	6-mo F-U	9-mo F-U	12-mo F-U
MINI DSM-5	1,S	substance use disorder	x					
HIV Rapid Antibody Test	1,S	HIV status		x				
*ASK-PrEP* Admission/Follow-up Assessment	1,S	demographics; individual-level characteristics; social/structural determinants		x	x	x	x	x
Timeline Follow-Back*****	1,S	Current substance use		x	x	x	x	x
NBA***** / NBA-Lite**	1,S, E	needs, barriers and facilitators						
PrEP Care Continuum	1,S, E	PrEP initiation, adherence, persistence; PrEP advancement		x	x	x	x	x
HIV-ASES	1	components of PrEP self-efficacy		x	x	x	x	x
DBS***	1,S, E	oral daily PrEP adherence and persistence		x	x	x	x	x
Urine Drug Screen	1,S	current substance use		x	x	x	x	x
HIV Ag/Ab and Viral Load Test	1,S, E	HIV seroconversion			x	x	x	x
Electronic Health Records	1,S, E	PrEP care, PrEP prescriptions, PrEP advancement, liver and kidney functions		x	x	x	x	x
DATCAP****	2	intervention cost		x	x	x	x	x
NMOS	2	resource costs		x	x	x	x	x
PROPr	2	HRQoL, QALYs		x	x	x	x	x
Locator Form	n/a			x	x	x	x	

*Administered during first PrEP navigation session only.

**Administered during all subsequent PrEP navigation sessions.

***With participants that report PrEP use only.

****Administered to study staff only.

*****Administered weekly, on Wednesdays, during the Contingency Management intervention.

#### Diagnostic and statistical manual-5 (DSM-5)

The DSM-5 assesses symptom criteria to ensure potential participants meet eligibility for a current SUD (mild, moderate, or severe). Findings are used to describe the sample, control for SUD severity, and examine the effect of SUD(s) severity as it pertains to advancement along the PrEP Care Continuum.

#### Rapid HIV antibody test

Potential participants are administered a rapid HIV antibody test (> 95% sensitivity, > 99% specificity) [59] during the screening process to verify HIV negative status. If the test is reactive, the potential participant is referred for additional evaluation and treatment.

#### ASK-PrEP admission/follow-up assessment

The full assessment is administered at baseline, and an abbreviated version is administered at all follow-up time points. The assessment collects demographics, substance use history, housing status, food security, educational attainment, HIV sexual risks, family and social history, legal status, incarceration history, sexually transmitted infections, hepatitis history, intimate partner violence, and gender confirmation procedures (for trans women participants only).

#### Timeline follow-back (TLFB)

TLFB [60] measures self-reported frequencies, quantities, and routes of administration of substances used. The TLFB is administered at baseline and at all follow-up time points with a 14-day recall period, and weekly with a 7-day recall period, alongside urine drug screens for those stepped to CM.

#### Needs and barriers assessment (NBA)

The NBA identifies behavioral health cofactors that may impede one’s ability to initiate and adhere to PrEP care (e.g., housing instability, poverty, transportation, legal restrictions, etc.). The NBA is administered during the *A.S.K.-PrEP* sessions to assist PrEP navigators with developing individualized participant-centered treatment plans, including SUD treatment options, to assess progress through the PrEP Care Continuum, and to reset priorities and identify possible new barriers. The shorter NBA-Lite is utilized in Sessions 2–5 to reassess needs and barriers as they change during intervention participation.

#### PrEP care continuum

In addition to biomarkers, participants self-report PrEP readiness: initiation, missed doses in the previous 4 days and 30 days (oral daily only), self-perceived ability to adhere, and structural-/individual-level barriers to adherence and persistence. The instrument includes three sections: (1) currently on PrEP, (2) formerly on PrEP, and (3) never on PrEP.

#### HIV Treatment Adherence Self-Efficacy Scale (HIV-ASES)

The HIV-ASES assesses participants’ self-efficacy to adhere to their HIV medication regimen (Cronbach’s alpha is routinely > 0.90) [61]. The HIV-ASES is lightly adapted to participants’ level of confidence that they can maintain PrEP adherence.

#### Dried blood spot (DBS)

DBS analysis for intra-erythrocytic TFV-DP (tenofovir-diphosphate; for participants using TDF or TAF-based PrEP) is performed by [name] laboratory at the University of Colorado, Denver to assess PrEP adherence. Results provide an assessment of average weekly adherence to oral TDF/FTC or TAF/FTC over the past 60–90 days (r2 ≥ 0.96 when regressed against plasma) [62]. No biomarker of Cabotegravir adherence is required, rather documentation of attendance at the clinic visit and administration of the injection at 2-month intervals is sufficient confirmation of adherence, given that the injection is directly observed.

#### Urine drug screen

Urine samples are collected via a 12-panel FDA-approved urine test cup by Confirm Biosciences, San Diego, CA to capture current use of various drug at varying detection times and concentration cut-offs: amphetamines (2–4 days, 1,000 ng/mL), barbiturates (4–7 days, 300 ng/mL), buprenorphine (103 days, 10 ng/ML), benzodiazepines (3–7 days, 300 ng/mL), cocaine (2–4 days, 300 ng/mL), methamphetamine (3–5 days, 1,000 ng/mL), MDMA (1–3 days, 500 ng/mL), opiates/morphine (2–4 days, 2,000 ng/mL), methadone (3–5 days, 1,000 ng/mL), oxycodone (2–4 days, 100 ng/mL), phencyclidine (7–14 days, 25 ng/mL), and cannabis (2–30 days, 50 ng/mL) [63].

#### HIV testing via laboratory-based hiv antigen/antibody test

At all follow-up visits, participants are tested by a laboratory-based (performed on phlebotomized blood) antigen/antibody test as the primary assessment of HIV serostatus and HIV-1 RNA (100% sensitivity, 99.5% specificity). If a participant provides laboratory results via Electronic Health Records from a PrEP care visit in the previous 3 months, the laboratory-based HIV antigen/antibody test is forgone.

#### Electronic health records (EHRs)

Research assistants work with participants to show them how to access their EHR through their provider’s portal. EHRs are utilized to record HIV status, retention in PrEP care, PrEP prescriptions, kidney and liver function to ensure that PrEP is well tolerated, and viral load.

#### Drug abuse treatment cost analysis program (DATCAP)

Resources required to implement and sustain each intervention are identified via microcosting analysis, which will entail the collection of administrative data, whenever feasible, along with semi-structured interviews with relevant staff members. The microcosting analysis is guided by a tailored version of the DATCAP, a standardized, customizable tool designed to capture intervention resources in a manner conducive to estimating the associated costs, across diverse settings [64].

#### Non-study medical and other services (NMOS)

Utilization of healthcare services are self-reported using time-anchoring methodology via the NMOS form. Healthcare services encompass non-study: inpatient, outpatient, and emergency department; SUD treatment medications; residential and outpatient SUD treatment days; hospital SUD detoxification days; and mental health treatment visits. Use of non-medical and other resources required for the economic evaluation from state-policymaker and societal perspectives (e.g., criminal-legal, labor productivity, travel time to medical care) is also self-reported and collected via the NMOS.

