**Fig. 1 Fig1:**
[figure not shown]
Schematic of ASK-PrEP Stepped Care, Randomized Controlled Trial Design

The trial will recruit 250 HIV-negative trans women and SMM with an SUD (*n* = 83 trans women; *n* = 167 SMM); participants will be randomized (3:1) to *A.S.K.-PrEP* (*n* = 187), or Standard of Care (SOC; PrEP education, information, and referrals) (*n* = 63). Participants in the *A.S.K.-PrEP* Stepped Care arm will receive 5 PrEP navigation sessions within 3 months and will be assessed at 3-months for intervention response; responders will maintain the *A.S.K.-PrEP* intervention, while non-responders will be re-randomized (1:1) to either add attention to their SUD (*A.S.K.-PrEP* + CM), or shift attention to their SUD (CM alone). The study uses repeated assessments at baseline and at 3-, 6-, 9-, and 12-months post-enrollment; all assessments will be administered to participants regardless of their participation or retention. All intervention content is tailored to trans women and SMM with an SUD. Participants may choose to initiate daily oral PrEP (TDF/FTC or TAF/FTC) or long-acting injectable Cabotegravir [10].

The specific aims of the research include the following:

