#### Aim 2:

Estimate the cost of implementing and sustaining each intervention (Stepped Care with: a] *A.S.K.-PrEP* + CM; b] CM alone) and incorporate these costs into a comprehensive cost-effectiveness analysis to determine the value of each intervention relative to SOC, and to each other, from the healthcare-sector, state-policymaker, and societal perspectives.

#### Hypothesis 2

The Stepped Care approach with *A.S.K.-PrEP* + CM will be the most cost-effective intervention, despite its relatively high sustainment cost, due to its greater effectiveness resulting in larger improvements along the PrEP Care Continuum, and in SUD, thereby generating: (a) reduced utilization of high-cost healthcare, safety-net, and criminal-legal resources; and (b) increased productivity, time free from primary substance, and quality-adjusted life-years (QALYs). Stepped Care with CM alone will be the next best “value” for the same reasons.

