The outcome of the cost-effectiveness analysis is the incremental cost-effectiveness ratio (ICER), which is calculated as the incremental cost of a given intervention relative to an alternative, divided by the incremental mean effectiveness of the two interventions. The primary measure of effectiveness for the economic evaluation is QALYs; the second is advancement along the PrEP Care Continuum. The QALY is a measure that combines the HRQoL associated with an individual’s health state and their time spent in that state, and is the foremost effectiveness measure in economic evaluation studies due to its comparability across interventions/disorders, and the existence of generally-accepted value thresholds [74, 76]. The PrEP Care Continuum is an important and widely accepted model/tool for assessing PrEP care outcomes at both an individual and a public-health level; thus, the additional cost required to achieve a one-step increase along the Continuum for the average trans woman or SMM with an SUD, has important clinical and policy implications. Two ICERs (one for each effectiveness measure) are calculated for each stakeholder perspective at both 6 months (intervention completion; immediate effects) and over the 12-month observation period (intervention + follow-up).

ICERs consist of predicted mean cost and effectiveness values. To help address censored data we model the person period and estimate all regressions using a multivariable generalized linear mixed model (GLMM) [74]. Separate multivariable GLMMs are estimated to predict the mean dollar value for each resource, the health utility value, and PrEP Care Continuum steps gained at each time period, by study arm. Predicted mean costs and steps gained are then be summed and tested over the relevant time periods (6 months, 12 months), and QALYs gained are estimated using the predicted health utility values and the area under the curve methodology, then tested [74]. Standard errors are estimated via nonparametric bootstrapping techniques within the multivariable framework. Methods to reduce bias from participant attrition and missingness are combined within the non-parametric bootstrap, following recommended approaches [67].

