### Limitations

There are several challenges to the *A.S.K.-PrEP* clinical trial. First, substance use, housing instability, engagement in sex work, and other individual-level, social, and structural disparities may interfere with study participation. To address this, the first level of the *A.S.K.-PrEP* intervention in the Stepped Care approach was designed to reduce/remove barriers and link participants into behavioral health services. Second, episodes of short-term incarceration can impact study participation and follow-up assessment rates. Due to actual or perceived participation in the street economy and/or minor infractions, study participants may experience cycles of brief incarceration. Study staff monitor the LAC public records database for participants who miss appointments. When an incarcerated participant is found, we begin a mail correspondence with the individual. Third, some participants may lack identification necessary to obtain PrEP. The PrEP navigators help participants fill out documentation and accompany them to the Department of Motor Vehicles to get a free or low-cost ID with a wavier form. Fourth, most participants do not have health insurance, including Affordable Care Act coverage. Again, the PrEP navigators and the partnering PrEP care clinics assist participants with enrollment in public or private insurance or patient assistance programs. Some participants may lose or sell their oral-daily PrEP due to lifestyle needs (“diversion”). In recognition of this, PrEP adherence is stressed through a participant-centered treatment plan, including an analysis of how PrEP adherence outweighs selling PrEP. Furthermore, this study is conducted in an urban setting on the West Coast and may not be representative of the HIV and substance use co-epidemic, and the impacted communities in other regions of the United States. Additionally, due to limited resources, substance use frequency is only assessed with a 14-day recall period at each follow-up assessment visit, and weekly with a 7-day recall period for those re-randomized into the Contingency Management intervention. Finally, the sample may also be subject to self-selection bias, namely trans women and SMM who are more receptive to participating in a clinical trial or receiving services for HIV prevention and substance use reduction.

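### Criminal-legal use is recorded only by self-report at assessment visits, which incarceration can itself prevent, so Aim 2 risks understating this cost

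*Protocol article*

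**What the plan says.** - **Source of the data.** The Measures section on the NMOS lists non-medical resources ("e.g., criminal-legal, labor productivity, travel time to medical care) is also self-reported and collected via the NMOS") and ties them to the state-policymaker and societal perspectives. No administrative source is named. For healthcare use the same section says "Utilization of healthcare services are self-reported using time-anchoring methodology via the NMOS form"; it gives no recall window.
- **Timing.** Under Fig. 1, "The study uses repeated assessments at baseline and at 3-, 6-, 9-, and 12-months post-enrollment"; Table 4 places the NMOS at each of these. Also, "all assessments will be administered to participants regardless of their participation or retention".
- **Threat to follow-up.** Limitations says that "episodes of short-term incarceration can impact study participation and follow-up assessment rates".
- **Custody search.** Limitations adds: "Study staff monitor the LAC public records database for participants who miss appointments". The only stated next step is to write to a participant found in custody.
- **Analysis.** Statistical analysis/outcomes, Specific Aim 2: "To help address censored data we model the person period and estimate all regressions using a multivariable generalized linear mixed model (GLMM"). It adds further methods against attrition and missingness bias inside the bootstrap, without naming them or their covariates.
- **Hypothesis.** Hypothesis 2 expects "reduced utilization of high-cost healthcare, safety-net, and criminal-legal resources".

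**The concern.** The event being costed is one that the article itself names as a possible reason for its cost not being recorded. A participant in jail at an assessment date may complete no NMOS for that period. Unless the stay is reported later, the jail days are absent from the data.

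A person-period GLMM handles missing periods under a missing-at-random assumption: given what was observed, missed and attended periods are taken to be alike. That fails if being jailed makes a missed visit more likely. Weighting or imputation built only on visit data shares the weakness, because a participant's free periods do not reveal a jailed one.

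At stake are the criminal-legal component of the state-policymaker and societal ICERs, their acceptability curves, and the part of Hypothesis 2 that predicts lower criminal-legal use. Aim 1 is not involved.

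**Working it through.** The article gives no incarceration rate, missed-visit rate or unit cost, so there is no stated figure to reproduce. Every rate below is an assumption. The quantity is the share of person-quarters with incarceration, not dollars.

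**Check 1: level of incarceration.** Inputs:
- q = share of quarters missed: 10% to 30%
- r0 = incarceration share in attended quarters: 5%
- r1 = incarceration share in missed quarters: 10% to 30%
- h = share of missed quarters recovered by recall at a later visit: 0, 0.5 or 1

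Formulas:
- True share = (1−q)·r0 + q·r1
- Estimated share with no custody information = [(1−q)·r0 + q·h·r1] / [(1−q) + q·h]

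Central case, q = 0.20 and r1 = 0.20:
- True: 0.80×0.05 + 0.20×0.20 = 8.0%
- h = 0: estimated 5.0%, understated by 1 − 5.0/8.0 = 38%
- h = 0.5: (0.04 + 0.02)/0.90 = 6.7%, understated by 17%
- h = 1: estimated 8.0%, understated by 0%

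| Case | True | h = 0 | h = 0.5 | h = 1 |
|---|---|---|---|---|
| q 10%, r1 10% | 5.5% | 9% under | 4% under | 0% |
| q 20%, r1 20% | 8.0% | 38% under | 17% under | 0% |
| q 30%, r1 30% | 12.5% | 60% under | 25% under | 0% |

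The bias is also 0% if r1 = r0, that is, if missed quarters carry no excess incarceration.

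**Check 2: the level by another route.** Let j be the true share of periods with jail, mj the chance of a missed visit if jailed, and m0 = 15% the chance if not. The share seen among attended periods is j(1−mj) / [j(1−mj) + (1−j)(1−m0)]. With j = 10%:
- mj = 15%: 100% of the true share is recovered
- mj = 30%: 84%
- mj = 50%: 0.050/(0.050 + 0.765) = 6.1%, so 61%
- mj = 80%: 25%

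If later recall bridges the missed periods at mj = 50%, recovery goes from 61% (none bridged) to 83% (half) and 100% (all).

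**Check 3: difference between arms.** Same formula, with true shares of 15% in SOC and 10% in Stepped Care, a true difference of 5.0 points:

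| mj in SOC | mj in Stepped Care | Observed difference (points) |
|---|---|---|
| 30% | 30% | 4.3 |
| 50% | 50% | 3.3 |
| 80% | 80% | 1.4 |
| 50% | 30% | 9.4 − 8.4 = 1.0 |
| 30% | 50% | 12.7 − 6.1 = 6.6 |

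With equal missingness the difference shrinks. With unequal missingness it can shrink further or be exaggerated.

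The setup of Check 1, with both incarceration shares halved in Stepped Care and r1 = 20% in SOC, shows shrinkage only. With 20% missed in both arms the difference shrinks by 38% (h = 0) or 17% (h = 0.5). With 25% missed in SOC and 15% in Stepped Care it shrinks by 51% or 21%; with those rates reversed, by 13% or 8%. That setup holds the excess of incarceration in missed quarters at the same ratio in both arms, so it cannot show the exaggeration seen in Check 3.

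**The case against.** The strongest reply is that a condensed article is being read for what it omits. The GLMMs are multivariable with no covariate list, further attrition methods are promised, and the visit assessment collects incarceration history. Custody status may enter the full analysis plan. This stands in part: nothing says that custody status is excluded, and missing model detail is not a fault here. But incarceration history is also self-reported at visits, so it does not cover a missed period. The data source for criminal-legal use is fixed in the article, and custody findings that are not recorded as staff search may be hard to recover later.

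The second reply is that the stays are described as brief. Someone released before the next assessment can report them then. This stands: with no recall window given, the loss may be none, partial or full.

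A reader might infer more than the documents support:
- **That the model fills jailed periods purely from other people who attended.** A mixed model also uses the participant's own other periods and covariates.
- **That incarceration is shown to cause missed visits.** Limitations says only that it can affect follow-up.
- **That the saving is necessarily attenuated.** Check 3 gives 6.6 points observed against 5.0 true when jailed Stepped Care participants are missed more often. No missed-visit rates by arm are given.
- **That the ICERs are shown to be wrong.** No ICER effect can be calculated, and criminal-legal use is one of several resources in the two perspectives concerned.

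**Conclusion.** The concern holds as a risk built into the data source, not as a demonstrated error. It requires two things together: jailed participants miss assessments more often than others, and later visits do not recover all of the missed stays. Where both hold and custody status is left out of the models, mean criminal-legal cost is likely understated. The bias in the between-arm difference has no fixed direction.

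On the assumed rates, the understatement of incarceration runs from 0% to about 60%, with 38% (no later recall) or 17% (half recovered) in the central case. Confidence in the size is low. Only the state-policymaker and societal ICERs are in question; the healthcare-sector ICERs are not shown to be affected. The change is worth making because staff already look up the relevant information for the people concerned.

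**What to change.** 1. For every missed assessment in both arms, with the search done blind to arm, record the custody status found in the county public records search, and the dates where the source gives them. The article does not say that the database holds booking and release dates.
2. Use custody status as an auxiliary variable in the missingness models, and use the records to fill incarceration for person-periods that no NMOS covers.
3. State the NMOS recall window. At the next attended visit, ask about any period not yet covered.
4. Report the state-policymaker and societal ICERs with and without these data.

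The cost is modest: data-entry fields, wording in the analysis plan, and a search that must cover every missed assessment systematically. With data collection expected to run to April 2027, a change made during follow-up can still help. Downsides: the county database misses custody elsewhere, two sources are mixed for one resource, and the consent wording must be checked to cover this use.
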